In a pilot study of the FICare program conducted at Mount Sinai Hospital, Toronto, 31 FICare infants were matched 1:2 with control infants (*n* = 62) based on gender, gestational age (± 2 weeks), birth weight (± 300 grams), age at enrollment, and length of stay following enrollment of ≥ 21 days. The rate of change in weight gain was significantly higher in FICare infants compared with control infants (*p* < 0.05). There was also a significant increase in the rate of breastfeeding at discharge (82.1 vs. 45.5 %, *p* < 0.05). The mean Parental Stress Scale: NICU (PSS:NICU [32]) score for FICare mothers was 3.06 ± 0.12 at enrolment, which decreased significantly to 2.30 ± 0.13 at discharge (*p* < 0.05) compared with control mothers, whose stress scores were not significantly reduced (3.25 ± 0.19 at admission, 2.99 ± 0.2 on discharge, *p* > 0.05). Feedback regarding program implementation from the parents and nurses was very positive [33].

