### Outcomes and measures

The primary outcome of the trial is weight gain at 21 days since enrollment in the program, as measured by the z-score [38]. The z-score refers to the exact number of standard deviations greater or smaller than the median, and is used to monitor the growth of the infant relative to the expected intrauterine growth rate. It is standardized to population growth standards and superior to percentiles for infants whose size is outside of the normal range of a growth chart. As part of standard NICU practice infants are weighed at the same time each day with their diaper removed. Many infants are weighed on special scales built into their incubator. To decrease any risk of measurement bias nurses/parents are asked to first recalibrate the scales, then weigh the infant three times, and take the average weight. The bedside nurse charts the infant’s weight as per usual practice.

The secondary outcomes are: i) weight gain velocity at 21 days since enrollment and weight gain velocity from birth to 36 weeks corrected gestational age; ii) parent stress and anxiety; iii) breastfeeding rate at hospital discharge; iv) clinical outcomes including NICU mortality and major neonatal morbidities; v) safety as indicated by the number of critical incident reports per 1000 patient days; and vi) resource use including duration of oxygen therapy, duration of hospital stay, and potential cost savings due to reduced length of stay estimated using per diem costs [39].

The major neonatal morbidities include ≥ stage 2 necrotizing enterocolitis (NEC) defined according to Bell’s criteria [40]; bronchopulmonary dysplasia (BPD) defined as oxygen dependency at 36 weeks postmenstrual age or at the time of transfer to a level 2 centre [41]; nosocomial infection (NI) defined using the Center for Disease Control criteria [42]; ≥ stage 3 retinopathy of prematurity (ROP) classified according to the International Classification [43]; and ≥ grade 3 intraventricular hemorrhage (IVH) defined according to the criteria of Papile et al. [44] from cranial ultrasound during the first 28 days of life.

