In both the intervention and control sites, parental stress and anxiety are measured using questionnaires (PSS:NICU and the State Trait Anxiety Index [STAI]) administered to parents at enrollment (Day 0) and Day 21 following enrollment. The PSS:NICU is a validated instrument to measure parents’ perceptions of stress within the NICU [32]. It comprises a 46-item self-report instrument that consists of four subscales that measure stress related to the: a) sights and sounds of the unit, b) appearance and behaviour of the infant, c) impact of the parents’ role and their relationship with their infant, and d) parents’ relationship and communication with the staff. The STAI is the definitive instrument for measuring anxiety in adults [45]. It is well validated, simple to use, and available in 40 languages. The STAI Form Y comprises of 40 items that can be completed in about 10 min, and measures state and trait anxiety. It provides a measure of the severity of the overall anxiety level.

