### Statistical analysis

The unit of analysis will be the individual infant, and all analyses will be based on the intention to treat principle. The distribution of baseline characteristics in the study population will be summarized at the individual and cluster level within each FICare and control groups, using descriptive statistical methods. The primary outcome of weight gain at 21 days post enrollment, will be compared between the FICare and control groups using Student’s *t*-test adjusted for the inflation factor (or design effect) with a minimum variation weight correction [46, 47] to account for intra-cluster correlation and imbalance of cluster sizes. In addition, a two-level hierarchical linear regression model will examine the primary outcome, accounting for clustering, and potential confounders including patient-level characteristics (birth weight, gestational age, small for gestational age, gender, multiple births, admission illness severity, caesarean section, chorioamnionitis, maternal hypertension or diabetes, maternal education, parity) and NICU-level covariates (NICU size, teaching institution).

Secondary outcomes will be compared between the FICare and control groups using similar methods including the Student’s *t*-test for continuous variables and the Chi-square test for categorical variables adjusted for clustering [50, 51], as well as hierarchical linear or logistic regression models, as appropriate. Furthermore, weight change over time will be examined longitudinally using multivariable multi-level hierarchical models to compare the rate of change in weight gain between infants from the two trial arms.

While we realize that multiple comparisons are a concern when more than one analysis of the data is performed, we are not interested in the joint confidence region for all of our hypotheses at once. Rather, we are interested in them one at a time. Under these conditions, Rothman and Greenland [52, 53] argue that “multiple inference procedures … are irrelevant, inappropriate and wasteful of information” because they produce improperly imprecise single intervals.

Prior to data unmasking and analyses, issues relating to missing data and potential sources of bias will be examined and appropriate correction methods determined.

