To assess selection bias, differences in the enrolment rate at FICare and control sites will be examined. Multivariable analyses will correct possible confounding bias by adjusting for baseline factors including social, economic (parental education, employment), demographic (maternal age, family size), obstetric (parity, pregnancy complications) and infant factors (gestational age, small for gestational age, illness severity at admission, and age at enrollment). Further analyses will consider propensity score methods accounting for imbalance of baseline characteristics between FICare and control groups [54]. While we will attempt to identify and adjust for all the possible confounding variables, we also acknowledge that any selection/participation bias could be due to some unmeasured element of “parent engagement” at the initiation of the intervention.

Subject attrition may also produce biased results and impact generalizability. Families in the FICare group are provided with as much physical, psychological and financial support as possible (including parent lounge; subsidized parking or a transit pass; access to peer-to-peer, social, and psychiatric support services), but no such supports are available to control families. Attrition bias will be minimized by performing statistical analyses according to the intention to treat principle. To minimize losses due to retro transfer from level 3 to level 2 units prior to completion of the 21-day trial period, the original study protocol has been amended to allow follow-up of these infants within level 2 units provided these units obtain Research Ethics Board approval, receive appropriate training, and comply with the study protocol including providing nurse education and parent education programs.

Possible bias due to differential withdrawal or study drop-out will be assessed by examining the distribution of baseline factors between families who consent and complete the study, and eligible families who consent and start but do not complete the study within the intervention and control sites. Furthermore, a sensitivity analysis will compare results from complete-case data and from all families who were enrolled where missing data are imputed using methods that account for clustering [56, 57].

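### Parental stress and anxiety have a Day 0 score in both arms, but the stated comparison is a t-test without it and neither covariate list commits to it

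*Protocol article*

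**What the plan says.** The Outcomes and measures section lists "ii) parent stress and anxiety" among the secondary outcomes and does not say whether the endpoint is a level or a change. The same section has both questionnaires, PSS:NICU and STAI, "administered to parents at enrollment (Day 0) and Day 21 following enrollment", at intervention and control sites alike.

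For the comparison, the Statistical analysis section states: "Secondary outcomes will be compared between the FICare and control groups using similar methods including the Student’s *t*-test for continuous variables". The test is adjusted for clustering, and models are added: "as well as hierarchical linear or logistic regression models, as appropriate". No covariates are named for the parental outcomes.

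Two covariate lists appear in the article. The one in Statistical analysis is written for the primary outcome, infant weight gain, and covers "potential confounders including patient-level characteristics (birth weight, gestational age, small for gestational age, gender, multiple births, admission illness severity" with further obstetric, maternal and NICU-level items. The one in Limitations and feasibility reads "Multivariable analyses will correct possible confounding bias by adjusting for baseline factors including social, economic (parental education, employment), demographic (maternal age, family size" and goes on to obstetric and infant factors. Both are open lists, introduced by the word *including*. Neither names the Day 0 PSS:NICU or STAI score.

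**The concern.** The Day 0 score on the same questionnaire is usually the strongest single predictor of the Day 21 score. A t-test has no place for it as a covariate, whether it is run on Day 21 scores or on change.

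This matters more here than in an individually randomized trial. Limitations and feasibility explains that families are recruited after their site's allocation is known, by unblinded coordinators, and that consent differs by arm. Only intervention sites require a commitment of at least 6 h per day. The section itself expects that enrolled FICare families may have higher socioeconomic status or more family support, and both are plausibly related to stress and anxiety. Equal Day 0 scores therefore cannot be taken for granted.

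Parental stress and anxiety are a central part of the FICare rationale. If the comparison is not anchored to Day 0, part of a reported difference may reflect who was recruited, and its standard error is larger than the collected data require.

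**Working it through.** **The plan's own figure.** The article gives no effect size, power or sample size for parental outcomes. Its one calculation, 675 infants per arm, is for weight z-score change. It reproduces closely:
- Before clustering, n = (1.96 + 0.84)² × (0.57² + 0.43²) / 0.11² ≈ 331 per arm.
- With minimum-variance weights, ICC 0.01 and 3 large plus 5 small sites per arm sharing infants in the ratio 315:113, this becomes 625 evaluable infants.
- Allowing for 10% drop-out, 625 / 0.9 gives 695, within 3% of 675.

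This neither supports nor weakens the present point.

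**Inputs.**
- Measurement at Day 0 and Day 21 in both arms (Outcomes and measures).
- Pilot PSS:NICU means (Background and rationale): FICare mothers 3.06 falling to 2.30. Control mothers are those "whose stress scores were not significantly reduced (3.25 ± 0.19 at admission, 2.99 ± 0.2 on discharge".
- rho, the Day 0 to Day 21 correlation, is not in the documents. I assume 0.3, 0.5 and 0.7.
- Further assumptions: equal variance at the two times, and the same rho within and between sites.

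**Imbalance.** Let Y be the difference between arms at Day 21 and D the difference at Day 0. Under these assumptions the slope on baseline is rho.
- Adjusted contrast: Y − rho × D.
- Day 21 only: Y, which is the adjusted contrast plus rho × D.
- Change score: Y − D, which is the adjusted contrast minus (1 − rho) × D.

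For rho between 0 and 1, the two possible t-tests therefore depart from the adjusted contrast in opposite directions.

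**Precision.** Variance relative to a Day 21-only comparison:

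| rho (assumed) | Day 21 only | Change, 2(1 − rho) | Adjusted, 1 − rho² |
|---|---|---|---|
| 0.3 | 1 | 1.40 | 0.91 |
| 0.5 | 1 | 1.00 | 0.75 |
| 0.7 | 1 | 0.60 | 0.51 |

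Ignoring the negligible cost of estimating one slope, adjustment is never less precise than either alternative. Where the Day 21-only comparison has 80% power, power after adjustment is Φ(2.80 / √(1 − rho²) − 1.96), which gives 83.6%, 89.9% and 97.5%. The gain from 80% does not depend on the ICC, because the starting power is fixed by assumption.

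**Pilot illustration.**
- Final difference: 2.99 − 2.30 = 0.69.
- Starting difference: 3.25 − 3.06 = 0.19.
- Change contrast: 0.69 − 0.19 = 0.50.
- Adjusted: 0.69 − rho × 0.19 = 0.63, 0.60 and 0.56.
- Carried over from the start: rho × 0.19 = 0.057, 0.095 and 0.133, which is 8%, 14% and 19% of 0.69.
- If the ± values are standard errors (the article does not label them), the starting gap has SE √(0.12² + 0.19²) = 0.22 and is about 0.85 SE, within chance.

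The pilot's final score was taken at discharge, not Day 21, and its baseline is described as enrolment for FICare mothers but admission for controls. It shows the mechanism and does not predict the trial's gap.

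**The case against.** The strongest reply is that this is an omission in a condensed article and not an error. The first covariate list is for infant weight, where a parental score would not be expected. Both lists are open. Limitations and feasibility promises an attempt to adjust for all possible confounders and mentions propensity score methods, and Statistical analysis defers bias corrections to a step before unmasking. A separate analysis plan may name the Day 0 score. This stands in part: nothing in the article rules out Day 0 adjustment. But the article does choose a test and does enumerate its adjustment factors, and a better use of data already collected is available. Propensity methods are only to be considered, with no variables named.

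A reader might infer that any Day 0 difference passes in full into the reported effect. The article does not support that. It never says that Day 21 scores alone are tested. The primary outcome, to which the phrase about similar methods points back, is a change score, and a change score subtracts the raw gap. Even a Day 21 comparison departs from the adjusted contrast by rho × D, not by D. For the same reason, reading the pilot as 28% carry-over (0.19 / 0.69) would need a slope of 1.

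Two further objections qualify the remedy:
- If the arms differ by stable selection, baseline adjustment can under-correct and a change score may be the less biased choice. Preferring adjustment is then partly an assumption.
- According to the Enrollment section, intervention-site parents may attend education sessions whether or not they join the trial, and they hear of them before consent. The Day 0 score may thus already carry a little intervention effect, and adjusting for it could remove some of that.

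Neither objection removes the precision gain or makes the unspecified t-test the better main analysis.

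**Conclusion.** The point holds in a limited form. The stated t-test does not adjust for the Day 0 score on either reading, the hierarchical models are not committed to it, and the endpoint is not fixed as level or change. Relative to a baseline-adjusted contrast, a Day 0 gap D leaves +rho × D or −(1 − rho) × D depending on that unstated choice, and the recruitment process makes such a gap plausible.

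Adjustment would cut the variance of a Day 21 comparison by 9% to 49% for rho from 0.3 to 0.7. At rho 0.3 the power gain from 80% is under 5 points; at 0.5 it is about 10. These sizes rest on an assumed rho and on comparison with the t-test, not with the covariate-adjusted model that is also planned. The documents do not show that a gap exists in this trial or what size it would have. The change is worth making for a named secondary outcome; confidence is moderate.

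**What to change.** In Statistical analysis, state that the main between-arm comparison of Day 21 PSS:NICU and STAI is the hierarchical linear model with the Day 0 score of the same scale as a covariate (state and trait anxiety each with their own Day 0 value) and a random NICU effect. Keep the cluster-adjusted t-test as descriptive, and say whether it uses the Day 21 score or the change. In Limitations and feasibility, add the Day 0 scores to the baseline factors for these parental outcomes.

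Report the change-score contrast as a sensitivity analysis, since adjustment may not fully remove stable selection differences. Note that Day 0 may follow some exposure to education sessions at intervention sites.

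The cost is wording, because the scores are already collected. Families without a Day 0 questionnaire would need the clustered imputation that the article already plans as a sensitivity analysis.

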### Limitations and feasibility

A cluster randomized trial design was selected to evaluate FICare as it is an organizational and behaviour intervention where blinding of participants or investigators is not possible. Cluster randomized controlled trials are more effective at preventing contamination, but more susceptible to biases than trials randomizing individual subjects [54, 55]. In this trial, possible allocation bias is being minimized by the use of appropriate study design methods for cluster randomization including stratification (sites within each country randomized separately; big and small sites in Canada randomized separately) with randomization performed using a random number generator.

Selection bias may arise due to prospective recruitment of families after randomization of NICU sites, and differences in the nature and process of obtaining informed consent. Study coordinators who recruit families are not blinded to their site’s allocation and families consent to participate in rather than be randomized to the FICare intervention or control protocol. At intervention sites, consent is given to participate in the FICare program and to complete study questionnaires and collect infant data, whereas, at control sites consent is given for questionnaire completion and data collection only. Notably, the inclusion criteria at FICare sites require a time commitment of ≥ 6 h, whereas families at control sites are not specifically asked if they would be able to make the same commitment. As such, participants at intervention sites who commit to FICare may differ from those at the control sites, who do not have to commit to spending extended time in the NICU. For example, families who enroll in FICare may be at a higher socioeconomic level or have greater family support than control families.

To assess selection bias, differences in the enrolment rate at FICare and control sites will be examined. Multivariable analyses will correct possible confounding bias by adjusting for baseline factors including social, economic (parental education, employment), demographic (maternal age, family size), obstetric (parity, pregnancy complications) and infant factors (gestational age, small for gestational age, illness severity at admission, and age at enrollment). Further analyses will consider propensity score methods accounting for imbalance of baseline characteristics between FICare and control groups [54]. While we will attempt to identify and adjust for all the possible confounding variables, we also acknowledge that any selection/participation bias could be due to some unmeasured element of “parent engagement” at the initiation of the intervention.

Subject attrition may also produce biased results and impact generalizability. Families in the FICare group are provided with as much physical, psychological and financial support as possible (including parent lounge; subsidized parking or a transit pass; access to peer-to-peer, social, and psychiatric support services), but no such supports are available to control families. Attrition bias will be minimized by performing statistical analyses according to the intention to treat principle. To minimize losses due to retro transfer from level 3 to level 2 units prior to completion of the 21-day trial period, the original study protocol has been amended to allow follow-up of these infants within level 2 units provided these units obtain Research Ethics Board approval, receive appropriate training, and comply with the study protocol including providing nurse education and parent education programs.

Possible bias due to differential withdrawal or study drop-out will be assessed by examining the distribution of baseline factors between families who consent and complete the study, and eligible families who consent and start but do not complete the study within the intervention and control sites. Furthermore, a sensitivity analysis will compare results from complete-case data and from all families who were enrolled where missing data are imputed using methods that account for clustering [56, 57].

Recognizing the limitations of the cluster randomized controlled trial design, we have planned to thoroughly examine factors that may confound the effect of FICare with infant and parental outcomes, to correct analyses for bias when feasible, and to report possible residual bias.

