### Study participants

Eligible study infants include those who are: i) born at ≤ 33 weeks’ gestation; and ii) on no respiratory support or on low-level respiratory support (i.e., oxygen by cannula or mask, or non-invasive ventilation such as continuous positive airway pressure [CPAP], biphasic CPAP and nasal intermittent positive pressure ventilation). As most infants born at ≤ 33 weeks’ gestation are not discharged home until at least 36 weeks’ postmenstrual age, a minimum “dose” of 3 weeks of in-hospital intervention is ensured. An additional inclusion criterion at the intervention sites is that the primary caregiver parent must commit to spending a minimum of 6 h per day with her/his infant between the hours of 7 am and 8 pm to enable attendance at medical rounds and education sessions.

Infants excluded from the study are those who: i) are receiving palliative care; ii) have a major life-threatening congenital anomaly; iii) have a critical illness and are unlikely to survive; iv) are on a high level of respiratory support (mechanical ventilation, high-frequency oscillatory or jet ventilation, extra-corporeal membrane oxygenation); v) are scheduled for early transfer to another hospital; or vi) have parents with an inability to participate (e.g., health, family, social, or language issues that might inhibit their ability to integrate with the health-care team).

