### Enrollment

Parental consent is being obtained from families of eligible infants at both the intervention and control sites. For NICUs randomized to the FICare intervention arm, the site program coordinator approaches parents of all potentially eligible infants soon after admission to the NICU to explain the study verbally and deliver an information leaflet detailing the purpose and process of the study, as well as any possible detrimental effects of participation. Parents are screened to determine if there are barriers to their participation in the trial, and informed of the FICare education sessions, which they may attend regardless of whether they participate in the trial. Parents are then approached for informed consent when their baby becomes eligible (i.e., stable on CPAP). Families are enrolled in the trial, after consent is obtained (Day 0). All families approached are recorded in a patient eligibility log regardless of actual participation. Infants whose parents decline to participate in the study receive standard care at that site.

For NICUs randomized to the control arm, the site program coordinator approaches the parents of all potentially eligible infants for consent to collect infant data and information on parental stress and anxiety. The families of eligible infants at control sites are not screened to determine whether they would be willing to spend at least 6 h per day in the NICU as per the FICare protocol. The infants of parents who consent are enrolled in the study once they meet the inclusion criteria, and continue to receive standard care.

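### The named adjustment covariates date illness severity to admission and omit respiratory support at Day 0, an earlier measure of BPD and oxygen duration that eligibility already requires

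*Protocol article*

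**What the plan says.** In the protocol article, Statistical analysis, the two-level model for the primary outcome adjusts for birth weight, gestational age, small for gestational age, and "gender, multiple births, admission illness severity, caesarean section, chorioamnionitis, maternal hypertension or diabetes, maternal education, parity", together with NICU size and teaching status. For the other outcomes, "Secondary outcomes will be compared between the FICare and control groups using similar methods", with hierarchical linear or logistic models where suitable. No separate covariate list is given for BPD, oxygen duration or length of stay.

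Limitations and feasibility gives a second list, meant to deal with selection bias: "Multivariable analyses will correct possible confounding bias by adjusting for baseline factors including social, economic (parental education, employment", followed by demographic and obstetric factors and then "infant factors (gestational age, small for gestational age, illness severity at admission, and age at enrollment". The same section adds "While we will attempt to identify and adjust for all the possible confounding variables" and says that propensity score methods will be considered.

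Study participants admits infants who are "on no respiratory support or on low-level respiratory support". The examples run from oxygen by cannula or mask, through CPAP and biphasic CPAP, to nasal intermittent positive pressure ventilation; infants on mechanical ventilation are excluded. Under Enrollment, Day 0 is the day the family enters after consent. Outcomes and measures defines BPD as still needing oxygen at 36 weeks' postmenstrual age or on transfer to a level 2 centre, and lists "resource use including duration of oxygen therapy, duration of hospital stay".

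**The concern.** In this trial admission is not baseline. An infant is enrolled when stable enough, at a variable interval after admission. Two infants with the same gestational age and the same admission severity can start follow-up in room air and on nasal ventilation respectively. Age at enrollment is a Day 0 variable and partly reflects the time taken to reach eligibility, but it does not say which level of support the infant is on.

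For BPD and oxygen duration, Day 0 support is an earlier reading of the same respiratory status, and adjusting for such a baseline is ordinary practice. Two things are at stake. One is efficiency: a smaller residual variance for oxygen duration, and better power for BPD. The other is bias. Sites were randomized first and families recruited afterwards by coordinators who know the allocation, so randomization does not guarantee a similar support mix at entry. The protocol relies on covariate adjustment to deal with this, so what the list contains matters. A difference in mix at entry could be read as a benefit or a harm of FICare.

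**Working it through.** The point concerns covariate choice, and the plan has no figure of its own to reproduce. The check is a comparison of sections, followed by an illustration of scale.

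**1. What the named covariates capture**

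| Item | Statistical analysis list | Limitations and feasibility list |
|---|---|---|
| Illness severity | at admission | at admission |
| Age at enrollment (Day 0) | not named | named |
| Respiratory support at Day 0 | not named | not named |

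**2. Whether the value is available.** Study participants makes respiratory support both an inclusion and an exclusion criterion, so the site must know it when the infant is enrolled. Data collection adds that charts are abstracted daily from enrollment.

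**3. Whether it varies.** Yes. Eligible infants run from no support to nasal ventilation, giving four natural levels: none, oxygen, CPAP or biphasic CPAP, and nasal ventilation. Four levels need three indicator terms.

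**4. Whether it relates to the outcomes.** BPD and oxygen duration are later measures of the same status by the protocol's own definitions. For length of stay the link is clinical inference, reasonable but not stated.

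**5. Whether it could differ by arm.** Limitations and feasibility says recruiting coordinators know their site's allocation, and that only intervention-site families must commit to at least 6 h a day. This is a route to imbalance. It is not evidence that imbalance occurred.

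**6. Scale, with assumed inputs.** None of these values comes from the documents. Let d be the difference between arms in the share of infants on the higher level of support, and let r1 and r0 be the BPD risks at the higher and lower levels. The shift in the BPD risk difference with no effect of FICare is d × (r1 − r0).

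| d | r1 = 30%, r0 = 10% | r1 = 40%, r0 = 5% |
|---|---|---|
| 5 points | 0.05 × 0.20 = 1.0 point | 0.05 × 0.35 = 1.75 points |
| 10 points | 0.10 × 0.20 = 2.0 points | 0.10 × 0.35 = 3.5 points |
| 15 points | 0.15 × 0.20 = 3.0 points | 0.15 × 0.35 = 5.25 points |

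With 30% against 2%, a 10-point imbalance gives 0.10 × 0.28 = 2.8 points. If d = 0 the shift is zero.

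These are crude shifts. The planned models adjust for gestational age and admission severity, and where age at enrollment is included for that too. To read the table as residual bias, d and r1 − r0 must be the differences that remain within levels of those covariates. The documents give neither.

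**The case against.** The document is a journal article. It may leave the full covariate set for each secondary outcome to an analysis plan that is not shown. Both lists are introduced as examples rather than as complete, the authors say they will try to adjust for all possible confounders, and they promise to examine sources of bias before unmasking. So Day 0 support is not excluded. That stands, and the right word is unnamed, not excluded. But the authors chose to name covariates in detail twice, dated severity to admission both times, and a general promise does not supply this particular variable.

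A reader might go further in four ways that the documents do not support.

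- That the strongest predictors of these outcomes are missing. The documents rank no predictors.
- That adjustment rests on admission status alone. The quoted list itself contains age at enrollment.
- That the arms use different entry rules, because intervention families are approached "when their baby becomes eligible (i.e., stable on CPAP" and control infants enter once criteria are met. The respiratory criterion is the same in both arms, and the CPAP phrase is a gloss on becoming eligible.
- That mother's milk at Day 0 should likewise be a covariate for breastfeeding at discharge. The article does not say it is recorded. Intervention units have trained staff and breast pumps, and their parents may attend education sessions whether or not they join the trial. Milk at Day 0 may therefore already reflect FICare, and adjusting for it could remove part of the effect.

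A milder version of that last caution applies to respiratory support too: it is measured after site randomization, in units already assigned to an arm.

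**Conclusion.** The point holds in limited form. The named covariates describe severity at admission and, apart from age at enrollment, do not capture the infant's state at Day 0. Respiratory support at Day 0 should be named for BPD and oxygen duration, where it is an earlier measure of the outcome, and for length of stay on clinical plausibility. The outcomes concerned are secondary, and the primary analysis is not called into question here.

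The size is not known. The illustrative range of about 1 to 5 points in the BPD risk difference rests wholly on assumed imbalances of 5 to 15 points and assumed risks by support level, and it makes no allowance for the adjustment already planned. The case for the change rests on the value being already established and closely tied to the outcome, not on evidence that the arms differ.

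**What to change.** - Add respiratory support at Day 0 (none / oxygen / CPAP or biphasic CPAP / nasal ventilation) to the prespecified covariates in the adjusted models for BPD, duration of oxygen therapy and length of stay.
- Show it by arm in the baseline table.
- Because it is measured after site randomization, report the results without this covariate alongside. For BPD, make that comparison on the risk-difference scale or with standardized risks: an odds ratio can change when a predictive covariate is added even if the arms are balanced.
- Do not make mother's milk at Day 0 a covariate in the main model for breastfeeding at discharge. At most, report it by arm if it is recorded.

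The cost is wording in the analysis plan, one baseline-table item and up to three more parameters per model. Support is already established for eligibility, so no new assessment is needed.
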